### Statistical methods

#### Analysis

Analysis will be performed for an intention-to-treat population consisting of all randomized participants regardless of their actual treatment received. Any missing data will be replaced with ones by a multiple imputation technique [25]. All data will be analyzed descriptively. Of the primary and secondary outcome measurements, variables of FDI, H-B grade and stiffness scale are discrete ordinal variables whereas lip mobility is recorded as a continuous variable. For primary and secondary outcome measurements, the mean differences from the baseline values to the end of treatment will be compared between the two groups using the two-sample t-test if the data are distributed normally. In case of non-normally distributed data, Wilcoxon rank-sum test will be performed. If baseline values of outcome measurements are significantly different between groups, analysis of co-variance (ANCOVA) will be performed using any imbalanced variables as covariates and assigned group as fixed factor.

All adverse events reported during the study will be included in the clinical report, and the prevalence of adverse events will then be calculated. The percentage of subjects with adverse events in each group will be calculated and compared using the chi-squared test or Fisher's exact test.

Statistical analyses will be performed using the SAS statistical package program (ver. 9.1.3), and the level of significance will be established at α = 0.05.

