### Secondary outcome

Secondary outcome measures will include FDI-social score from baseline to week five, FDI-physical score, House-Brackmann (H-B) Grade [15], lip mobility (lip-length and snout indices) [16], and stiffness scales [17]. The H-B grade has been tested for its reliability [18] and lip-length and snout indices showed a high correlation with H-B Grade [19]. Stiffness scale is a simple five-point scale for facial stiffness (1 = no stiffness, 5 = very stiff) [17].

Unfortunately, there has been no validation study of Korean version of each of the primary and secondary outcomes. In our study, two professional translators made each outcome measurement questionnaire in Korean, which has been used in our clinical facial palsy center for evaluating sequelae of facial palsy. So we decided that these questionnaires are readable and suitable to our study.

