### Eligibility

#### Inclusion criteria

To be included, patients have to be diagnosed with Bell's palsy at least six months prior to screening. Patients must score less than 70 on the physical aspect of the FDI, less than 80 on the social aspect and provide written informed consent. Participants who are 18 to 65 years old will be recruited using local newspaper advertisements and posted notices.

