#### Sample size

Sample size was calculated from the result of a mime therapy trial conducted on patients with sequelae of Bell's palsy of which design was randomized parallel waitlist controlled trial [17]. We assumed that the effect size of our invasive acupuncture therapy will be at least equal to this non-invasive mime therapy. Also we decided the allocation ratio to be 2:1 with the consideration that fewer patients should be allocated to the waitlist group.

In the mime trial, the mean difference of follow-up FDI-social score between groups was 14.5 and pooled standard deviation was 14.5 within each group [17]. The alpha value and power were 0.05 and 0.8 respectively. From these values we calculated sample size for independent two sample t-test (one-tailed) that is 26 for acupuncture group and 13 for waitlist group with consideration of 20% drop-out. And this assumed mean difference of FDI-social score between groups is considered to be sufficiently important in an expert discussion consisting of clinicians who work in Bell's palsy clinics for more than 10 years.

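### H-B grade and stiffness, classed as ordinal, are analysed as unadjusted change from baseline; the week-8 grade, always adjusted for baseline grade, would be more efficient and clearer to read

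*Protocol article*

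**What the plan says.** Secondary outcome section: "Secondary outcome measures will include FDI-social score from baseline to week five, FDI-physical score, House-Brackmann (H-B) Grade", followed by lip mobility and stiffness. On the last of these: "Stiffness scale is a simple five-point scale for facial stiffness (1 = no stiffness, 5 = very stiff").

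Analysis section:
- Scale type: "variables of FDI, H-B grade and stiffness scale are discrete ordinal variables whereas lip mobility is recorded as a continuous variable".
- One rule for all primary and secondary outcomes: "the mean differences from the baseline values to the end of treatment will be compared between the two groups using the two-sample t-test", provided the data are normal.
- Fallback: "In case of non-normally distributed data, Wilcoxon rank-sum test will be performed".
- Baseline adjustment: "If baseline values of outcome measurements are significantly different between groups, analysis of co-variance (ANCOVA) will be performed", with the imbalanced variables as covariates.

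Inclusion criteria: "Patients must score less than 70 on the physical aspect of the FDI, less than 80 on the social aspect". No minimum H-B grade or stiffness score is required.

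**The concern.** The plan calls the two scales ordinal and then subtracts one grade from another. A move from 5 to 4 on the stiffness scale counts the same as a move from 2 to 1, and the average of such differences has no clear unit. The fallback does not change this on its natural reading, because the Wilcoxon test then ranks the same differences. A patient who enters at stiffness 1 can only contribute a zero or a worsening, and the entry criteria do not exclude such patients.

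The second issue is efficiency. Subtracting the baseline grade is not the same as adjusting for it. The plan adjusts only after a significant baseline difference. In a randomised trial tested at 0.05, that happens for a given outcome in about 5% of trials, so these grades would nearly always be analysed without adjustment. The trial has 39 participants and was sized for FDI-social alone, so the secondary outcomes have little power to spare.

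**Working it through.** **1. The plan's own figure.** The Sample size section reports that "the mean difference of follow-up FDI-social score between groups was 14.5 and pooled standard deviation was 14.5 within each group", so the standardised difference is 14.5/14.5 = 1.0. With one-sided alpha 0.05, power 0.8 and 2:1 allocation, the waitlist arm needs (1 + 1/2) × (1.645 + 0.842)² / 1.0² = 1.5 × 6.185 = 9.28, so 10, and the acupuncture arm 20. A noncentral-t calculation gives the same numbers (power 0.81). Dividing by 0.8 for dropout gives 12.5 and 25, which is 13 and 26 when 2:1 is kept. The stated size reproduces. It concerns FDI-social; no power is stated for H-B grade or stiffness.

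**2. Why subtraction costs precision.** On an underlying scale with unit variance at both visits and correlation ρ, the change has variance 2(1 − ρ) and the baseline-adjusted week-8 value has variance 1 − ρ². The ratio of adjusted to change variance is (1 + ρ)/2: 0.70 at ρ = 0.4, 0.80 at 0.6, 0.90 at 0.8 and 0.95 at 0.9. The cost of subtracting shrinks as ρ rises.

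**3. Simulation on the grades.** Arm sizes are the protocol's, 26 and 13. The documents give none of the following, so they are assumptions: bivariate normal latent values; a latent shift of 0.8 SD; two-sided 0.05; H-B cut at cumulative proportions 2/25/60/88/98%; stiffness cut at 25/50/72/90%, so 25% start at no stiffness. Power in %:

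| Latent correlation | 0.4 | 0.6 | 0.8 | 0.9 |
|---|---|---|---|---|
| H-B: Wilcoxon on change | 43 | 57 | 80 | 92 |
| H-B: rank ANCOVA, week-8 grade | 63 | 70 | 86 | 95 |
| Difference (points) | 20 | 13 | 6 | 3 |
| Stiffness: Wilcoxon on change | 39 | 50 | 74 | 89 |
| Stiffness: rank ANCOVA, week-8 grade | 61 | 68 | 85 | 95 |
| Difference (points) | 22 | 18 | 11 | 6 |

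Repeats with 2,500 runs per setting at correlations 0.4 to 0.8 agree with each cell within about 4 points. In them:
- Type I error was 4.3 to 6.1% for all methods (Monte Carlo standard error √(0.05 × 0.95/2500) = 0.4 points).
- The t-test on change had 48/60/82% for H-B and 43/56/74% for stiffness, at or slightly above the Wilcoxon test.
- The Shapiro-Wilk test rejected normality of the changes in 65 to 100% of data sets, so the Wilcoxon branch would usually be taken.

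The conditional ANCOVA was not simulated.

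**4. Which feature causes the loss.** ANCOVA on the raw numeric grade also assumes equal steps. For H-B it had power 65/73/88/97% at the four correlations, at least as high as rank ANCOVA. For stiffness, a repeat gave 62/71/86% at 0.4/0.6/0.8. Equal spacing therefore costs nothing here; leaving out the baseline adjustment does.

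**5. Other assumptions.** A second set used 5 to 40% at the best grade, four or five grades, correlation 0.3 to 0.9, and a shift of 0.8 SD (0.5 SD at 0.85 and 0.9). Two equal-step methods can be compared directly there: ANCOVA on the raw grade exceeded the t-test on change in every case, by about 3 points (0.655 against 0.627) to 22 points (0.625 against 0.407). Baseline-adjusted proportional odds exceeded the t-test by about 7 to 24 points, but its likelihood-ratio test had type I error of 5.3 to 7.8% at this sample size, so part of that advantage is not real. A Wilcoxon test on the week-8 grade without the covariate is no remedy: at correlation 0.9 with 5% at the best grade, its power was 0.25 against 0.63 for the t-test on change.

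**The case against.** The strongest reply is that this is a preference between valid methods for two secondary outcomes. The planned tests hold their type I error, the plan has a rank-based fallback and a route to ANCOVA, and all data will also be described. No grade distribution, correlation or effect size for these scales is given. Patients are at least six months past diagnosis, so high stability over eight weeks is plausible, and at correlation 0.9 the loss is only 3 to 6 points. All of this stands, and it limits the size of the point. It does not remove it: adjustment was more powerful in every setting tried, and the ANCOVA route is rarely open.

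Some stronger readings are tempting but not supported:
- *The equal-step assumption destroys power.* Step 4 of the working shows otherwise.
- *Patients at the best grade are ignored.* The analysis covers all randomised participants, so they count. They cannot register improvement, and no analysis of the same scale changes that. How many there will be is unknown.
- *The only blinded evidence is weakened.* The Outcome measures section says the independent assessor is blinded, but not who rates which scale, so the blinded rating of H-B grade is an inference.

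The text also does not say outright that the Wilcoxon test is run on changes; that is the natural reading of the rule.

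**Conclusion.** The point holds as a modest, inexpensive improvement. Analysing H-B grade and stiffness as unadjusted change gives a summary without a clear meaning and gives up precision. Under the stated assumptions the loss against baseline-adjusted rank analysis is about 3 to 22 power points, decided mainly by the unknown correlation between baseline and week 8. A reader might infer that much of the power is certainly lost, or that the trial's main result is at risk. The documents support neither: the range rests on assumed inputs, the planned tests are valid, and FDI-social and the sample size are untouched. The efficiency argument is about baseline adjustment in general and is not peculiar to ordinal scales; the lack of a clear unit is what sets these two outcomes apart.

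**What to change.** In the Analysis section, take H-B grade and stiffness out of the common change-score rule. State that the week-8 grade will be compared between groups by rank ANCOVA, with baseline grade always included as a covariate whatever the baseline comparison shows. If a proportional-odds model is preferred, take its p-value from a permutation test, because its likelihood-ratio test can run above 5% with 39 participants. Add a table of baseline grade by week-8 grade for each group, which also shows how many started at the best grade.

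This costs a few sentences and a few lines of code, and needs no new data or patients. The downside is that the result no longer reads as a mean grade change; the shift table supplies the descriptive reading.

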### Primary outcome

The change in the Facial Disability Index (FDI) social [14] score after completing eight weeks of acupuncture treatment will be compared to the score prior to treatment. This scoring system consists of two domains; physical score and social score, and has been investigated for the reliability and validity [14]. FDI-social score evaluations will be performed on the first visit, the fifth- and eighth-week visits. Participants will answer five multiple choice questions related to problems associated with facial muscle function during the previous month.

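### The primary analysis depends on the data: baseline adjustment waits for a significant baseline difference, so no single primary estimate is fixed and some power may be lost

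*Protocol article*

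**What the plan says.** The Primary outcome section of the protocol article takes a before-and-after change in FDI-social as the endpoint ("The change in the Facial Disability Index (FDI) social [14] score after completing eight weeks of acupuncture treatment will be compared to the score prior").

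The Analysis section then gives three routes to the result:

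- The default: changes from baseline "will be compared between the two groups using the two-sample t-test if the data are distributed normally".
- The fallback: where normality fails, the plan moves to the Wilcoxon rank-sum test.
- The conditional adjustment, which the section words as follows: "If baseline values of outcome measurements are significantly different between groups, analysis of co-variance (ANCOVA) will be performed using any imbalanced variables as covariates". Treatment group is the other term in that model.

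The same section plans multiple imputation ("Any missing data will be replaced with ones by a multiple imputation technique") and classes FDI as a discrete ordinal variable. It sets the significance level ("the level of significance will be established at α = 0.05") without saying whether tests are one- or two-sided.

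The Sample size section works from the follow-up score: "the mean difference of follow-up FDI-social score between groups was 14.5 and pooled standard deviation was 14.5 within each group". It gives no baseline SD and no baseline/follow-up correlation.

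**The concern.** Groups are formed by randomisation, so any baseline difference is due to chance. A test of that difference says nothing about whether adjustment is useful. What matters is how strongly the first-visit score predicts the week-8 score, and that does not depend on the baseline p-value.

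The rule has two consequences. First, the change score is the default in nearly every trial. A change score assumes that a one-point baseline difference carries forward as exactly one point at week 8. Where the true slope differs from 1, a chance imbalance too small to trigger ANCOVA still shifts the estimate. Second, which quantity is reported as the primary result (a difference in mean change, a rank comparison or an adjusted mean difference) is settled only once the data are seen. In a 39-patient trial with 2:1 allocation, both deserve attention.

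**Working it through.** **1. The plan's own figure.** Inputs from Sample size: difference 14.5, SD 14.5, one-tailed 0.05, power 0.8, ratio 2:1, 20% drop-out. Waitlist n = (1 + 1/2) × (1.645 + 0.842)² × (14.5/14.5)² = 9.3, so 10, with 20 for acupuncture (power 0.81 by the noncentral t). Dividing by 0.8 gives 12.5, so 13, and 2 × 13 = 26. The stated 26 + 13 reproduces. It contains no baseline adjustment.

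**2. How often the switch fires.** Under randomisation a 5% baseline test is significant in about 5% of trials by construction, so about 95% of trials keep the change score.

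**3. What the switch lets through.** With 26 v 13, the largest non-significant baseline gap is t(0.975; 37) × SD × √(1/26 + 1/13) = 2.026 × 0.340 × SD = 0.688 × SD.

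- Assumed baseline SD 14.5: 10.0 points.
- Assumed baseline SD 10: 6.9 points.

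The slope of week-8 on baseline is r × 14.5 / (baseline SD). The change-score difference is shifted by (1 − slope) × gap, in favour of the arm that starts lower when the slope is below 1:

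| Baseline SD | r | Slope | Shift at the largest missed gap (points) |
|---|---|---|---|
| 14.5 | 0.3 | 0.30 | 7.0 |
| 14.5 | 0.5 | 0.50 | 5.0 |
| 14.5 | 0.7 | 0.70 | 3.0 |
| 10 | 0.3 | 0.435 | 3.9 |
| 10 | 0.5 | 0.725 | 1.9 |
| 10 | 0.7 | 1.015 | about 0 |

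The planned effect is 14.5. These rows are the edge of what the switch misses, not a typical trial.

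**4. Power.** Simulation with normal data, true difference 14.5, week-8 SD 14.5, 20 v 10 analysed after drop-out, and two-sided 5%. The rule (ANCOVA only if baseline p < 0.05, otherwise a t-test on change) is compared with ANCOVA always fitted:

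| Baseline SD | r | Rule | ANCOVA always |
|---|---|---|---|
| 14.5 | 0.3 | 57% | 73% |
| 14.5 | 0.5 | 71% | 81% |
| 14.5 | 0.7 | 90% | 93% |
| 10 | 0.3 | 68% | 73% |
| 10 | 0.5 | 80% | 80% |
| 10 | 0.7 | 94% | 93% |

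The residual SDs explain the pattern. For change it is √(14.5² + s² − 2·r·14.5·s), with s the baseline SD; for ANCOVA it is 14.5·√(1 − r²). At r = 0.3 these are 17.2 v 13.8 for s = 14.5, and 14.9 v 13.8 for s = 10. At r = 0.7 and s = 10 they are equal (10.4 v 10.4).

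**5. Type I error.** At 26 v 13 with baseline SD 14.5, the rule's overall error is 0.042 to 0.045, slightly below 0.05. Among trials with baseline p between 0.05 and 0.20, where the switch stays off, the change-score test rejects a true null in 10.0/8.5/7.5% of trials at r = 0.3/0.5/0.7.

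**6. Normality choice.** The article names no criterion. With Shapiro-Wilk as an assumed one (26 v 13, r = 0.5, baseline SD 14.5), about 10% of truly normal data sets are flagged. The t-test and Wilcoxon verdicts differ in about 6% of trials under the alternative, and type I error stays near 0.05. Its cost is the unfixed estimate, not error rate or power.

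**The case against.** The strongest reply is that the damage may be small. The 14.5 SD is given for the follow-up score only. Entry requires FDI-social below 80 at screening, so the baseline spread may well be narrower, and at a baseline SD of 10 the power loss nearly disappears. This stands, which is why the size is given as a range. Power should also be judged on the plan's own one-tailed basis: with equal SDs and 20 v 10, the rule then gives 70/82/95% at r = 0.3/0.5/0.7, below the planned 80% only at low r. That stands too. The sidedness of the final test is a separate matter.

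A reader might infer three stronger things that the document does not support:

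- *Chance imbalance goes uncorrected.* It does not. A change score subtracts baseline, and significant imbalance goes to ANCOVA. The fault is mis-correction of the non-significant part, which is over-correction when the slope is below 1.
- *The rule inflates false positives.* Overall it does not; the raised error in step 5 is conditional on a particular range of imbalance.
- *A formal normality test chooses the method.* None is stated. The criterion, and the order of the rules when data are both non-normal and imbalanced, are details that an article may leave to an analysis plan.

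On imputation, a rank-sum test gives no estimate and standard error for the usual pooling rules, but rank-based quantities can be combined and the article specifies no pooling method. This is secondary.

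Finally, the article calls FDI ordinal, so a linear model should not simply displace the rank test. The fix allows for that. The reply does not rescue the baseline switch: it is stated in the text, and an analysis plan that follows the text would inherit it.

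**Conclusion.** The concern holds in a limited form. The protocol lets a baseline significance test and the look of the data decide the primary analysis. In about 95% of trials this leaves a change score that mis-corrects chance imbalance whenever the slope is not 1, and it fixes no single primary estimate. Those points need no assumption about power.

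The power loss ranges from about 16 percentage points (r = 0.3, baseline SD 14.5) to nil (r = 0.5 to 0.7, baseline SD 10). The shift at the largest missed imbalance ranges from 7.0 points to about 0. Both ranges rest on assumed r and baseline SD, normal data and a two-sided 5% test. There is no overall type I inflation and no error in the stated sample size. This is something that should be fixed because the improvement is nearly free; it does not invalidate the trial.

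**What to change.** In the Analysis section, name one primary analysis: ANCOVA of week-8 FDI-social on group, with first-visit FDI-social as covariate, fitted whatever the baseline comparison shows. Report the adjusted mean difference with its 95% confidence interval, pooled over the imputations.

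Delete the baseline significance trigger and the choice between t-test and Wilcoxon by distribution. Because the article classes FDI as discrete ordinal, keep a rank-based analysis as a pre-specified sensitivity analysis.

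The first-visit score is already collected, so no new data are needed. The cost is one degree of freedom and a few sentences.

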#### Sample size

Sample size was calculated from the result of a mime therapy trial conducted on patients with sequelae of Bell's palsy of which design was randomized parallel waitlist controlled trial [17]. We assumed that the effect size of our invasive acupuncture therapy will be at least equal to this non-invasive mime therapy. Also we decided the allocation ratio to be 2:1 with the consideration that fewer patients should be allocated to the waitlist group.

In the mime trial, the mean difference of follow-up FDI-social score between groups was 14.5 and pooled standard deviation was 14.5 within each group [17]. The alpha value and power were 0.05 and 0.8 respectively. From these values we calculated sample size for independent two sample t-test (one-tailed) that is 26 for acupuncture group and 13 for waitlist group with consideration of 20% drop-out. And this assumed mean difference of FDI-social score between groups is considered to be sufficiently important in an expert discussion consisting of clinicians who work in Bell's palsy clinics for more than 10 years.

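### The sample size uses the SD of follow-up FDI-social scores, but the primary test compares changes from baseline, so the stated 80% power is not established for that test

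*Protocol article*

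**What the plan says.** Protocol article, Sample size: the planning values come from a mime therapy trial in patients with sequelae of Bell's palsy, in which "the mean difference of follow-up FDI-social score between groups was 14.5 and pooled standard deviation was 14.5 within each group". The remaining settings are "The alpha value and power were 0.05 and 0.8 respectively", a one-tailed two-sample t-test, and a 2:1 ratio. With 20% drop-out this gives 26 for acupuncture and 13 for the waitlist.

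Protocol article, Primary outcome: the endpoint is the change in FDI-social score from before treatment to the end of eight weeks.

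Protocol article, Analysis: for primary and secondary outcomes, "the mean differences from the baseline values to the end of treatment will be compared between the two groups", by two-sample t-test if the data are normal and by rank-sum test otherwise. ANCOVA is used only when baseline values differ significantly between groups.

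The article gives no SD of change, no baseline SD and no correlation between baseline and week 8. It does not say why the follow-up SD may stand in for the SD of change.

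**The concern.** A power statement belongs to a particular test on a particular variable. The variable sized here is the score at follow-up; the variable tested is the change. In a randomised trial the expected group difference is the same for both, so carrying over the 14.5 as the difference does no harm. The SD is another matter. The SD of a change depends on the baseline SD and on how strongly baseline and week-8 scores correlate, and it can be larger or smaller than the follow-up SD.

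At stake is whether 39 participants, with only 13 planned controls and 10 after the allowed drop-out, give the primary comparison the power claimed for it.

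**Working it through.** **Inputs.** From Sample size: difference 14.5, SD 14.5, alpha 0.05 one-tailed, power 0.80, ratio 2:1, drop-out 20%. From Primary outcome and Analysis: the tested variable is change from baseline. Not in the article, and therefore varied: the correlation r between baseline and week 8, and the baseline SD.

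**Step 1: reproduce the plan's figure.** With 20 v 10 evaluable, the noncentrality is (14.5/14.5) / sqrt(1/20 + 1/10) = 2.58 on 28 degrees of freedom. The exact one-tailed power is 0.809, and 20 v 10 is the smallest 2:1 design that reaches 0.80. For drop-out, 10/0.8 = 12.5, rounded up to 13, and 2 × 13 = 26. The stated 26 + 13 = 39 is reproduced, which confirms that 14.5 was the SD used.

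**Step 2: change score with equal SDs.** If both SDs are 14.5, the SD of change is 14.5 × sqrt(2(1 − r)). It equals 14.5 at r = 0.5, is larger below that and smaller above. The ANCOVA columns use a residual SD of 14.5 × sqrt(1 − r²) and one fewer degree of freedom. All rows are for 20 v 10, one-tailed 5%.

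| r | SD of change | Power, change score | ANCOVA residual SD | Power, ANCOVA |
|---|---|---|---|---|
| 0 | 20.5 | 55% | 14.5 | 81% |
| 0.3 | 17.2 | 69% | 13.8 | 84% |
| 0.4 | 15.9 | 74% | 13.3 | 86% |
| 0.5 | 14.5 | 81% | 12.6 | 90% |
| 0.7 | 11.2 | 95% | 10.4 | 97% |

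**Step 3: break-even.** At 20 v 10, power is 80% when the SD of change is 14.69. Setting 14.5 × sqrt(2(1 − r)) = 14.69 gives r = 0.49.

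**Step 4: unequal SDs.** In general, SD of change = sqrt(s² + 14.5² − 2 × r × s × 14.5), where s is the baseline SD. The break-even is r = (s² + 14.5² − 14.69²) / (2 × s × 14.5):
- s = 10: r = 0.33
- s = 12: r = 0.40
- s = 18: r = 0.61

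**Step 5: other conditions, equal SDs.** If all 39 are fully observed (26 v 13), the break-even falls to r = 0.32. If the final test is two-sided, the 20 v 10 break-even rises to r = 0.60. The Analysis section states only α = 0.05, without sidedness.

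**Step 6: what a larger SD would cost.** Keeping the one-tailed change-score test, equal SDs and 20% drop-out, 80% power needs 30 + 15 = 45 participants at r = 0.4 and 36 + 18 = 54 at r = 0.3.

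**The case against.** Four points can be made for the plan.

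*The arithmetic is right.* It is: 26 + 13 follows exactly from the stated inputs. The fault is that the SD describes a different variable from the one tested.

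*No shortfall is shown.* A reader might infer that the trial is underpowered. The article does not support that. Nothing in it places r below the break-even, power exceeds 80% above it, and complete follow-up would lower the break-even to 0.32. Nor can one say flatly that r must be about 0.5 or more, because that threshold needs equal SDs and no baseline SD is given. What stands is that the 80% rests on quantities the article does not state.

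*The entry limit.* A reader might argue that requiring an FDI-social score "less than 80 on the social aspect" weakens the correlation and so lowers power. That does not follow, because restricting entry also shrinks the baseline variance. Write follow-up as a + b × baseline + error, so that the variance of change is (1 − b)² × Var(baseline) + Var(error). With b and the error variance unchanged, a smaller baseline variance cannot increase it. As an illustration with assumed values, start from r = 0.4 and both SDs 14.5, then halve the baseline variance. The correlation drops to 0.295, but the SD of change falls from 15.9 to 14.6 and power at 20 v 10 is 80%. The entry limit should not be cited in support.

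*The change-score t-test is valid.* It is unbiased under randomisation, and one sentence giving a justified SD of change would close the gap. Both statements are correct. The case for ANCOVA is that it removes the dependence on an unknown correlation. The provision for ANCOVA after a significant baseline difference does not do this, because the unadjusted comparison of changes remains the default.

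**Conclusion.** The point holds as a mismatch between the sizing variable and the tested variable on the primary endpoint. The stated 80% power is not established for the stated test. Under equal SDs, a one-tailed 5% level and the article's own 20% drop-out, power runs from 69% at r = 0.3 to 95% at r = 0.7, and the break-even correlation moves between about 0.33 and 0.61 as the baseline SD goes from 10 to 18. Confidence is high in the mismatch. The size of its effect is uncertain in both directions, because the article supplies neither the correlation nor the baseline SD. It is worth correcting because the remedy needs no more participants.

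**What to change.** Make week-8 FDI-social, adjusted for baseline FDI-social by ANCOVA, the primary analysis without condition, and delete the rule that brings in ANCOVA only after a significant baseline difference. The residual SD then cannot exceed the planning value of 14.5, so the existing 26 + 13 supports about 81% power or more whatever the correlation, on the same one-tailed 5% and 20% drop-out basis.

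Baseline and week-8 scores are already collected, so no participants or visits are added. The cost is an amendment to the primary analysis. The article records a first randomisation on 04 August 2010, so the amendment should be made, and dated, before any outcome data are examined by group.

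If change scores are kept as primary, restate the power over a range of SDs of change, for example 17.2 down to 11.2 (r = 0.3 to 0.7 with equal SDs), and give the reason for the value chosen.
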